### Procedures - oxidative stress study

Oxidative stress will be analyzed on the first 15 patients in each group (for a total of 30 patients). Patients are sampled before surgery, before morphine bolus, and at 24 and 48 h after surgery.

Urine samples are directly aliquoted and stored at −80 °C; blood samples are collected in EDTA-containing vials and centrifuged within 30 min at 1000×*g* for 15 min at 4 °C to obtain the plasma.

Lipid peroxidation is analyzed through the determination of malondialdehyde with thiobarbituric acid assay in both plasma and urine. The 8-deoxyguanosine and poly(ADP-ribose) polymerase (PARP) are determined by commercial ELISA kits.

### Study outcomes

The primary outcome of the study is to investigate whether a wound infusion of local anesthetic and steroid has a higher analgesic efficacy compared with placebo during 7 days following surgery, assessed as analgesic consumption: the primary endpoint will be the reduction of morphine equivalents required in the first 7 days after surgery.

Secondary outcomes will include the differences in analgesia and side effects within 7 days after surgery. We will investigate any difference in pain at rest and movement (i.e., coughing and deep inspiration) by Numeric Rating Scale (11-point scale from 0 = no pain to 10 = worst imaginable pain), additional analgesic consumption, side effects (postoperative nausea and vomiting, sedation, and any signs of local anesthetic or steroid systemic toxicity), and incidence of persistent post-surgical pain. Differences in terms of wound healing or wound infections will be also assessed up to 3 months to assess any local side effect of steroid infusion. The degree of inflammatory response/oxidative stress between groups will be assessed to analyze the effect of CWI with either treatment or placebo. We plan to analyze the combined effect of some polymorphisms (by using a gene-candidate approach) of genes related to the development of PPSP, pain sensitivity, opioid response, and inflammatory reaction.

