### Procedures - clinical study

On the day of surgery, patients come to the operating room and are provided with standard monitoring (electrocardiogram, oxygen saturation, non-invasive blood pressure, and invasive pressure monitoring). General anesthesia is given using propofol and midazolam (as deemed appropriate by the anesthesiologist), opioids (fentanyl 0.2 μg/kg or remifentanil 0.1-0.25 mg/kg per min or both), and muscle relaxants (cisatracurium/rocuronium) and maintained with sevoflurane.

A morphine bolus of 0.15 mg/kg is given 30 to 45 min before the end of surgery. An infusion catheter (Baxter Painfusor®; Baxter International, Deerfield, IL, USA) is placed by the surgeon in the fascial plane between peritoneum and fascia trasversalis, and a 10-ml bolus of 0.2 % ropivacaine is administered immediately after muscular plane closure; the catheter is then connected to an electronic pump (CADD®-Solis; Smiths Medical, Dublin, OH, USA) to give a continuous infusion of pain medications.

During the first 24 h, all patients receive ropivacaine 0.2 % + methylprednisolone 1 mg/kg, 10 ml/h (total volume of 240 ml in 24 h) continuous wound infusion; additionally, either acetaminophen 1000 mg or ketorolac 30 mg every 8 h is prescribed.

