### After 24 h, patients are randomly assigned between two groups of treatment:

Treatment group: 10 ml/h continuous infusion of ropivacaine 0.2 % + methylprednisolone 1 mg/kgPlacebo group: 10 ml/h continuous infusion of saline 0.9 %.

Regardless of treatment group, rescue analgesia in the first 48 h is provided by PCA pump with morphine (0.5 mg/ml, bolus 1 mg, lock-out 5 min, 20 mg limit every 4 h).

Random group allocation of patients is made through a computer-generated sequence. To maintain blinding, a research fellow who is not taking part in patient evaluation is in charge of preparing and programming all of the pumps used during the study: an opaque, sealed, sequentially numbered envelope is assigned to each patient and is opened by the same research fellow after the first 24 h of treatment.

Patients and their anesthesiologists are blind to treatment assignment. A clinical resident, who is not involved with randomization, is in charge of all clinical evaluations as part of the daily clinical practice.

The envelope is maintained apart from the patient’s case report form and is to be opened in every potentially harmful situation for the patient but only when care providers need to be aware of the patient’s treatment. All ropivacaine and methylprednisolone vials used during the study are registered with their code in order to be tracked and recognized in the future for any issue potentially hindering the validity of data.

At 48 h, morphine PCA is removed, and all patients are treated with Patient-Controlled Intrawound Analgesia (PCA through the wound catheter) with either ropivacaine 0.2 % alone or saline according to the group of randomization up to a maximum of 7 days after surgery. The catheter is removed at the seventh postoperative day or after 36 h of non-use (no self-administered bolus). After PCA removal, rescue additional analgesia is provided by tramadol (100 mg or 50 mg according to patient’s weight of not more than or of more than 50 kg).

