All patients are evaluated at the end of surgery, at 3, 6, 12, 24, 36, and 48 h, and daily to the seventh postoperative day or until catheter removal by the Acute Pain Service and twice a day by the surgeons as part of their current clinical practice. Pain values, analgesic consumption, any drug-related side effect, and any catheter-related complication (such as occlusion or dislodgment) are recorded. Patients are also evaluated by surgeons after discharge, as in the current practice: any infection or healing retardation is monitored, together with any pain or sensorial abnormality to be signaled to the pain practitioners. Regardless, the Acute Pain Service investigates pain persistence at 1 and 3 months through a phone call, and patients with PPSP (patients experiencing pain at 1 or 3 months after surgery) are eventually referred to our pain clinic for evaluation and treatment.

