### Statistics

Sample size calculation was made on the hypothesis that the average morphine equivalent consumption in patients receiving local anesthetic and steroids CWI will be reduced by 50 % as compared with those in the control group. This assumption comes from (1) our retrospective experience and audits about analgesic consumption in our institution and (2) data from previous literature [27]; they both showed reduction in morphine consumption of 30–50 % in patients receiving local anesthetic wound infusion. Given this assumption, we need 50 patients per group for a power of 80 % and an α error of 5 %; given an attrition rate of 15–20 %, 120 patients are needed in each group.

We will perform an intention-to-treat analysis, and all participants will be analyzed once enrolled. We consider a “dropout” to be any patient not completing the evaluation at 3 months (for any reason).

For descriptive variables, we plan to use mean and standard deviation for normally distributed variables and average interquartile range for skewed distributions.

We will perform group comparison by using the Student’s *t* test or Mann–Whitney test for quantitative variables and Pearson’s chi-squared test for categorical variables. Inflammation, oxidative stress, and genetic background will be assessed to see whether they are biological markers that help modulate post-operative and persistent pain: the difference in inflammatory response and oxidative stress will be analyzed by means in a uni- and multi-variate regression model for repeated measures, including time, group, and their interaction. Variables will be transformed if needed to satisfy model assumptions. Post-hoc comparisons will include within-group changes over time and between-group differences at each assessment. The *P* value will be adjusted for multiple tests. Fisher exact test will be used to evaluate the impact of genetic background. The odds ratio and 95 % confidence interval will be computed with logistic regression. The *P* value to assess statistical significance will be corrected with the Bonferroni correction depending on the number of candidate genes tested.

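### Secondary analgesia and side-effect outcomes are counted from surgery, 24 h before allocation, so shared early events weaken a 7-day side-effect comparison, and pain too if early scores are included

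*Protocol article*

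**What the plan says.** The protocol article fixes four things that bear on each other.

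- **Run-in.** Procedures - clinical study: "During the first 24 h, all patients receive ropivacaine 0.2 % + methylprednisolone 1 mg/kg, 10 ml/h".
- **Allocation.** The next section begins: "After 24 h, patients are randomly assigned between two groups of treatment".
- **Outcome window and schedule.** Study outcomes: "Secondary outcomes will include the differences in analgesia and side effects within 7 days after surgery". These include pain at rest and on movement, additional analgesic use, nausea and vomiting, sedation and signs of toxicity. On the schedule: "All patients are evaluated at the end of surgery, at 3, 6, 12, 24, 36, and 48 h, and daily to the seventh postoperative day". These visits may stop earlier, when the catheter comes out.
- **Analysis.** Statistics gives Student's t "test or Mann–Whitney test for quantitative variables and Pearson’s chi-squared test for categorical variables". No covariate is named. A longitudinal model is described for the biomarkers only: "the difference in inflammatory response and oxidative stress will be analyzed by means in a uni- and multi-variate regression model for repeated measures", with time, group and interaction as terms.

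The Discussion recognises that a common first day might be questioned. It answers that the primary endpoint is analgesic consumption at 7 days and that any significant difference in morphine use at 24 h will be examined. It says nothing comparable about pain scores or side effects.

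**The concern.** Whatever happens in the first 24 h happens under one treatment and before any group exists, so it can differ between arms only by chance. A patient who vomits at 6 h is a case in a 7-day incidence whichever arm is drawn later, and nothing after 24 h can change that. Such patients raise the incidence in both arms, shrink the difference and bring both proportions into a range with more sampling variance.

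This matters most for safety. The article says the trial is meant to evaluate safety as well as efficacy and to clarify the balance of risk and benefit of the steroid infusion. A side-effect comparison pulled toward no difference can miss a real one, in either direction.

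The 24 h pain score is a natural baseline that is already collected, and the stated tests make no use of it.

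**Working it through.** **Stated figures.** The article gives no sample size or power for secondary outcomes. Its 50 per group at 80 % power concerns the primary endpoint and cannot be reproduced, because no standard deviation is given. At two-sided 5 % it implies a standardised difference of √(2/50) × (1.960 + 0.842) = 0.560, used below only as a calibration. I take 60 per arm from the total of 120 in the Abstract and Discussion. Statistics puts 120 in each group, but 100/0.85 = 118 and 100/0.80 = 125 support 120 as a total.

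**1. Side effects scored as ever in 7 days.** Let q be the shared incidence before 24 h, and a and b the incidences after 24 h in the two arms, taken to apply also to patients without an early event.

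- 7-day incidence = 1 − (1 − q)(1 − a), and likewise for b.
- Difference = (1 − q)(a − b).
- Power = Φ{[difference − 1.96·√(2p̄(1 − p̄)/n)] / √[(p₁(1 − p₁) + p₂(1 − p₂))/n]}, where p̄ is the mean of p₁ and p₂.

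The article gives no incidences, so a = 30 %, b = 10 % and the range of q are assumptions; n = 60.

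| q | 7-day incidences | Difference | Power |
|---|---|---|---|
| 0 % | 30 v 10 % | 20 points | 79 % |
| 10 % | 37 v 19 % | 18 points | 60 % |
| 20 % | 44 v 28 % | 16 points | 45 % |
| 40 % | 58 v 46 % | 12 points | 26 % |

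For q = 20 %: p̄ = 0.36, null standard error √(2 × 0.36 × 0.64/60) = 0.0876, alternative standard error √[(0.2464 + 0.2016)/60] = 0.0864, and Φ[(0.16 − 0.1718)/0.0864] = Φ(−0.136) = 0.45.

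For a rare sign, q is near zero and the factor (1 − q) is near 1.

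**2. Pain.** Counting days 3 to 7 after the 48 h visit, there are 12 assessments: 5 at or before 24 h (end of surgery, 3, 6, 12, 24 h) and 7 after (36 h, 48 h, days 3–7). The article does not say how scores are summarised. The share of a constant later difference that is kept is:

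- unweighted mean of all 12: 7/12 = 58 %;
- time-weighted mean over 7 days: 6/7 = 86 %;
- comparison by visit from 36 h: 100 %.

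For scale, set the effect so that post-24 h scores alone give 80 % power at 50 per group. Assume correlations of 0.3 to 0.7, between all scores for the unweighted mean and between the early and later averages for the time-weighted one. Power is then 41 % to 38 % for the unweighted mean and 75 % to 70 % for the time-weighted mean.

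**3. Additional analgesic use.** Write the 7-day total as A (0–24 h) + B (after 24 h). The expected difference in A is zero, so the expected absolute difference in the total equals that in B. The variance is Var(A) + Var(B) + 2Cov(A, B), larger than Var(B) unless A and B are strongly negatively related. The absolute effect is kept; precision and the relative difference fall.

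**The case against.** Much of this could be called analysis-plan detail: the pain summary, the covariate and the onset window for side effects are often settled there, and the 7-day phrase may mark only the end of follow-up. The t or Mann–Whitney rule is general and is not assigned to pain by name. Unadjusted tests after randomisation remain valid. That stands for the covariate, which is an efficiency gain, and for the pain summary, which is open. It does not dispose of the window, which the article states and counts from surgery although it places allocation a day later.

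A reader might infer that every secondary comparison is diluted. The document does not support that:

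- persistent pain is asked at 1 and 3 months, wholly after allocation;
- wound healing and infection are followed to 3 months;
- the biomarkers have a time-by-group model with comparisons at each assessment;
- pain compared from 36 h contains no early data.

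Nor may the 58 % be combined with a multiplicity charge. Fourteen tests (rest and movement at 7 later visits) would give 1 − 0.95¹⁴ = 51 % if independent, but testing by visit is exactly the reading with no dilution. Scores within a patient are not independent, and Statistics promises adjusted P values, although that sentence follows the biomarker model and its reach is unclear.

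The incidences are assumed, and scoring as ever in 7 days is the natural reading of the stated window rather than a stated rule.

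**Conclusion.** The point holds for the secondary 7-day outcomes. Their window includes 24 h that treatment cannot affect, the named tests do not allow for it, and the Discussion's check covers morphine only.

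- **Side effects:** the loss is real for common events such as nausea. The difference falls by the factor (1 − q), and power from 79 % to 45 % at q = 20 % and 26 % at q = 40 %, under the assumed 30 % v 10 % and 60 per arm. For rare toxicity signs it is small.
- **Pain:** anything from no loss to 42 % of the difference, depending on a summary the article does not name.
- **Analgesic use:** lost precision only.

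One might read this as favouring the treatment. It does not: a null comparison stays null, and a true difference in either direction is made smaller or harder to see. Persistent pain, wound outcomes to 3 months and the biomarker model lie outside the point.

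**What to change.** State in the outcomes and statistics text that:

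1. between-group side effects and additional analgesic consumption are counted from the switch at 24 h, with a rule for symptoms already present then;
2. events in the first 24 h are described for all patients together;
3. pain at rest and on movement from 36 h to day 7 is analysed with the 24 h score as covariate, for example in the model already planned for the biomarkers ("regression model for repeated measures, including time, group, and their interaction").

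The assessments are already scheduled by time, so this changes analysis wording and not data collection. With 46 patients enrolled and the trial still running, it can be settled before the groups are compared. There is one cost: acute pain assessments may stop at catheter removal, which depends on bolus use, so the model needs a stated way to handle scores missing after removal.

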In regard to local side effects, the main concerns are about wound healing and infections potentially associated with immune-modulatory action of steroids. Most of the existing data deal with high doses of systemic steroids [29, 30]. Up to now, few studies have addressed these issues in patients receiving peripheral steroids: these studies are in the orthopedic setting and investigate only clinical effects of a single-shot administration and provide no evidence of increased infections or difficult healing [29, 30]. We therefore plan to clarify the risk/benefit ratio of continuous administration of methylprednisolone, strictly monitoring wound healing and any potentially harmful effect of CWI.

We decided to treat all the patients with 24-h CWI of ropivacaine and methylprednisolone. This will enlarge the sample size for the phase III trial (120 patients) and will allow us to investigate the differences in locally released cytokines according to suspension of local anti-inflammatory treatment after the first 24 h. This, in our opinion, does not configure a methodological bias, as our primary endpoint is analgesic consumption at 7 days, and we will take care to evaluate any statistically significant difference in morphine consumption at 24 h to eliminate any confounding factor this kind of study design may potentially imply.

Furthermore, an ethical issue arises: because CWI with local anesthetics is already documented as a valuable analgesic strategy [8], switching to a saline infusion after 24 h in the control group may be questioned. Otherwise, placebo control is still a key feature for high-quality clinical trials in the perspective of determining the actual effectiveness of treatments. Furthermore, because we are investigating local inflammation, comparing analgesic efficacy with cytokine analysis will help clarify whether the pain-killing effect of CWI is associated either with methylprednisolone’s action or with a “washout” phenomenon (i.e., on the steroid’s effect on cytokine release rather than on cytokine dilution by fluid infusion).

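### The group difference in wound healing and infection cannot assess the local side effects of the steroid, because no arm is steroid-free and the arms also differ in ropivacaine up to day 7

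*Protocol article*

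**What the plan says.** All references are to the protocol article.

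- **Purpose of the wound outcome (Study outcomes).** Group differences in "wound healing or wound infections will be also assessed up to 3 months to assess any local side effect of steroid infusion". The sentence fixes both the measure (a difference between groups) and its target (local harm of the steroid).
- **0–24 h (Procedures - clinical study).** "During the first 24 h, all patients receive ropivacaine 0.2 % + methylprednisolone 1 mg/kg, 10 ml/h".
- **Randomisation (the section on assignment after 24 h).** "After 24 h, patients are randomly assigned between two groups of treatment". From then to 48 h one group continues ropivacaine plus methylprednisolone. The other receives "10 ml/h continuous infusion of saline 0.9" %.
- **48 h to day 7 (same section).** Patient-controlled wound infusion "with either ropivacaine 0.2 % alone or saline according to the group of randomization". Neither group receives steroid in this period.
- **Safety aim (Discussion).** "We therefore plan to clarify the risk/benefit ratio of continuous administration of methylprednisolone". The Abstract likewise presents safety as a purpose of the trial, and the Discussion lists the safety of topical methylprednisolone among the study's aims.
- **Defence of the shared first day (Discussion).** It "does not configure a methodological bias, as our primary endpoint is analgesic consumption at 7 days", supported by a planned check of morphine use at 24 h.
- **Test (Statistics).** Pearson's chi-squared for categorical variables. No safety margin and no external reference rate for wound events is described.

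**The concern.** The stated comparison does not identify the stated target. To learn what steroid infusion does to a wound, some patients must be unexposed, or a reference rate must be fixed in advance. Here both arms are exposed before randomisation, and after it the arms differ in two drugs rather than one.

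Wound harm from the first 24 h of methylprednisolone can occur in both arms and so need not appear in the difference. Systemic steroid effects counted within 7 days have the same problem, since part of that window lies before randomisation.

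The protocol describes this as the first phase III trial of continuous deep wound infusion of methylprednisolone and intends its results to inform delivery times and dosages for a new device. A safety statement resting on this contrast would be carried forward while answering a narrower question than the one written.

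**Working it through.** The protocol states no figure for wound outcomes, so there is none to reproduce. The point rests on exposure by period; the arithmetic only shows its size.

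**Step 1: exposure by period**

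| Period | Treatment group | Control group | Difference |
|---|---|---|---|
| 0–24 h (before randomisation) | ropivacaine + methylprednisolone | ropivacaine + methylprednisolone | none |
| 24–48 h | ropivacaine + methylprednisolone | saline | steroid **and** ropivacaine |
| 48 h to day 7 at most | patient-controlled ropivacaine | patient-controlled saline | ropivacaine |

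Steroid exposure is two 24 h periods against one, not some against none. Ropivacaine differs from 24 h up to day 7.

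**Step 2: how much harm the difference can show.** All rates here are assumptions, since the protocol gives none. Leave ropivacaine aside and let f be the share of the steroid's excess wound risk already caused by the first 24 h. With p0 the rate without steroid and pT the rate after the full course:

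- control-arm rate: pC = p0 + f × (pT − p0)
- visible difference: pT − pC = (1 − f) × (pT − p0)

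Take p0 = 10 %, pT = 20 % and 60 per arm (120 in total, as in the Abstract and Discussion). Power is for a two-sided 5 % comparison of two proportions by normal approximation: Φ{[(pT − pC) − 1.96·√(2p̄(1 − p̄)/n)] / √([pC(1 − pC) + pT(1 − pT)]/n)}, where p̄ is the mean of pC and pT. At f = 1 rejection occurs only at the 5 % error rate.

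| f | Control rate | Visible difference | Power, 60 per arm |
|---|---|---|---|
| 0 | 10.0 % | 10.0 points | 33 % |
| 0.5 | 15.0 % | 5.0 points | 11 % |
| 0.75 | 17.5 % | 2.5 points | 5 % |
| 1 | 20.0 % | 0 points | 5 % |

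Check at f = 0: p̄ = 0.15; 1.96 × √(2 × 0.15 × 0.85/60) = 0.128; √((0.09 + 0.16)/60) = 0.0645; (0.100 − 0.128)/0.0645 = −0.43; Φ(−0.43) = 0.33.

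For p0 of 5–15 % and a two- to threefold risk, f = 0.5 gives power of 7–40 % at 60 per arm. Statistics speaks of 120 in each group; at that size the range would be 10–67 %. At f = 1 no sample size helps.

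**Step 3: precision of a null result.** With 10 % in both arms and 60 per arm, the 95 % half-width of the difference is 1.96 × √(2 × 0.1 × 0.9/60) = 0.107, about 10.7 points. A non-significant chi-squared test would therefore leave a sizeable excess open even for the contrast that is randomised.

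**Step 4: what the exposed patients can tell.** An absolute rate with an exact interval is available whatever the comparator. With 0 events (an assumed count) in N patients, the exact two-sided 95 % upper limit is 1 − 0.025^(1/N):

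- N = 120: 3.0 %
- N = 102 (120 × 0.85): 3.6 %
- N = 96 (120 × 0.80): 3.8 %

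The last two apply the 15–20 % attrition in Statistics, where a dropout is a patient who does not complete the 3-month evaluation. That is also where wound follow-up ends.

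**The case against.** The strongest reply has four parts.

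- **The design is open.** The Discussion says that all patients are treated for 24 h and explains why. That stands, but the defence is tied to the analgesic primary endpoint. A check of morphine use at 24 h says nothing about wound events up to 3 months.
- **The comparison still has value.** It can reveal harm from a longer infusion, and the duration of infusion is a stated question. This stands. It supports describing the contrast as continuation beyond 24 h, not as the effect of steroid infusion.
- **The protocol never says that a non-significant difference will be taken as proof of safety.** This is correct. A reader might infer such a plan from the wording of the objective, but the text says only that differences will be assessed and wound healing strictly monitored. The fault is the mismatch between target and comparison, not a declared misreading.
- **Reporting detail belongs in an analysis plan.** This is partly fair. Exact intervals and period-specific tables could sit there. The objective itself, however, is worded in this document, and no analysis plan can make that contrast identify it.

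Two stronger readings also fail. A reader might infer that first-day harm cancels completely; that holds only if it adds equally in both arms. If risk rises with cumulative exposure, or the two days interact, part of it stays visible. A reader might also infer that the difference isolates the second steroid day; it does not, because ropivacaine differs between the arms from 24 h up to day 7.

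**Conclusion.** The concern holds in this form: the between-group difference in wound outcomes estimates the effect of continuing the active infusion beyond 24 h (a second steroid period plus continued ropivacaine) against switching to saline. It cannot assess every local side effect of steroid infusion. A null difference cannot show wound safety of the steroid, and an excess cannot be attributed to the steroid alone.

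This follows from the stated treatment schedule and needs no assumption. Its size does: the loss runs from none of the true excess (f = 0) to all of it (f = 1), and the documents do not fix f. The event rates and counts used above are illustrations. The pooled rate bounds absolute risk under exposure; it mixes one-period and two-period patients, has no unexposed comparator, and is not a steroid effect.

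The primary analgesic comparison is outside this point. The correction concerns a secondary outcome, but one that carries a stated safety aim.

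**What to change.** No change to treatment or data collection is needed.

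1. Reword the wound objective under Study outcomes as the effect on wound healing and infection of continuing the active infusion beyond 24 h (a second steroid period plus continued ropivacaine) versus switching to saline.
2. Report wound-infection and delayed-healing rates with exact 95 % confidence intervals by arm and pooled over all exposed patients. Give the number evaluable at 3 months, and state that the pooled rate bounds absolute risk and does not estimate a steroid effect.
3. Report side effects for 0–24 h pooled and after 24 h by arm. The scheduled evaluations at 3, 6, 12 and 24 h and later already allow this split.
4. State that safety against no steroid is not identified by this design, and that a non-significant group difference will not be read as absence of a steroid effect.

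The cost is a few lines of text, one extra table and a narrower safety claim.
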